## Abstract

**Background:**

Family caregivers of dying cancer patients are affected by grief experiences and bereavement complications. Several approaches such as psycho-emotional care and an increase in spirituality have been suggested to diminish these complications. However, the knowledge about the effects of family-based dignity intervention and expressive writing on anticipatory grief in family caregivers of dying cancer patients is limited. This is a study protocol describing a hospital-based mixed-methods study on the effects of family-based dignity intervention and expressive writing on anticipatory grief in family caregivers of dying cancer patients.

**Methods:**

This mixed-methods study will be done in an embedded explanatory design with two quantitative and qualitative phases. In the first phase (quantitative), a randomized clinical trial will be done, in which 200 family caregivers of dying cancer patients will be randomly assigned to one of the four groups: family-based single dignity intervention (group 1), expressive writing intervention (group 2), combined family-based single dignity intervention and expressive writing (group 3), and control (group 4). At baseline, 1 week and 2 weeks after the interventions, anticipatory grief will be assessed by a 13-item anticipatory grief scale. After the quantitative phase, the qualitative phase will be conducted through the conventional content analysis approach of Granheim and Lundman, in which an individual semi-structured interview will be taken from participants in the first phase to collect data on their experiences on interventions. Finally, data from the quantitative and qualitative phases will be analyzed and discussed.

**Discussion:**

Family caregivers of dying cancer patients usually experience depression, anxiety, and psychological distress due to isolation and inadequate social support. Psychological interventions such as dignity and expressive writing interventions may help caregivers to obtain a better understanding of themselves and to increase their abilities to cope with caregiving difficulties. Therefore, there is a need for a comprehensive study confirming the effects of mentioned interventions on family caregivers of dying cancer patients.

**Trial registration:**

Iranian Registry of Clinical Trials (www.irct.ir) identifier: IRCT20210111050010N1. Date of trial registration: Feb 6, 2021. This is the first version of this protocol.

**Supplementary Information:**

The online version contains supplementary material available at 10.1186/s13063-021-05718-3.

## Introduction

The diagnosis of cancer is an unpleasant and unbelievable experience for every person, and it imposes a high burden on the patient and his/her families [1–3]. As cancer progresses, patients became physically and psychologically weaker, and their dependency on family increases [4]. In addition to the dependency, the caregiving responsibilities of patients are often transferred to family caregivers who are usually spouses, adult children, mother, or father [4, 5]. Therefore, family caregivers, particularly those who take care of dying cancer patients, usually are confronted with several social, physical, and psychological difficulties, which may adversely affect their health [6, 7]. It has been shown that more than 35% of family caregivers experience psychological disorders and feelings of helplessness, hopelessness, and anticipatory grief [8, 9]. This is the reason that caregivers are considered as “second-order patients,” who need supportive care [10].

The religious culture of Iranian caregivers makes a strong relationship between caregivers and patients [11]. For this reason, caregivers look at their responsivities as moral commitment and divine duty [12]. Nevertheless, this religious belief may cause them to hide their needs and caregiving problems [13]. Moreover, there are no specific social organizations in Iran to support caregivers and to diminish their problems [14]. Therefore, family caregivers in Iran, compared with those from developed countries, may be at a higher risk of psychological disorders or anticipatory grief.

Anticipatory grief is one of the important problems among family caregivers [6]. They usually think about the threat of death or separation that can initiate a grief reaction, while the patient is physically present and needed of care [15]. Anticipatory grief is a “safeguard against the impact of a sudden death notice” that helps caregivers to cope with bereavement [16]. However, anticipatory grief is a highly stressful and ambivalent experience that may be a reason for the incidence of psychological distress among caregivers [17, 18]. In addition, this feeling may be transferred to patients and affect their treatment process. Therefore, caregivers should try to control their feelings and refrain from expressing grief for cancer patients [19, 20].

Several psychological interventions have been proposed to support caregivers in their challenges [10, 21–23]. Recently, it has been shown that family-based dignity intervention and expressive writing are effective approaches in the treatment of psychological disorders [10, 24]. Family-based dignity intervention is a spiritual-psychological intervention taken from dignity therapy methods [25]. This supportive intervention helps caregivers to strengthen the sense of hope in themselves and give them an opportunity to talk about their successes, aspirations, and plans [26]. Expressive writing intervention includes sessions of solitary and unlimited writing about positive and negative feelings and experiences caused by stressful events [27, 28]. Overall, talking about successes, aspirations, plans, and also expressing feelings through writing is an appropriate strategy to enhance well-being and may promote the ability of caregivers to cope with chronic grief.

Limited data are available on the effects of family-based dignity intervention and expressive writing on anticipatory grief in family caregivers of dying cancer patients. In addition, most studies assessing the effects of mentioned interventions had been done with a quantitative or to a lesser extent with a qualitative research methodology that both contain several limitations and strengths [10, 29, 30]. Mixing the qualitative and quantitative methods can cover the limitations and bring together the strengths of both methods [31, 32]. Recently, mixed-methods methodology, defined as mixing both qualitative and quantitative methodologies, has been introduced and has captured the interest of healthcare researchers [33]. The mixed-methods approach in interventional studies helps researchers to assess the experiences of participants throughout the intervention period, and in this way, researchers can present a better conclusion than the quantitative-only and qualitative-only research approaches [33, 34]. Therefore, in the current mixed-methods study, we will first conduct a four-arm randomized controlled trial to assess the effects of (1) combined family-based dignity intervention and expressive writing, (2) family-based dignity intervention alone, (3) expressive writing alone, and (4) routine care on anticipatory grief of family caregivers of dying cancer patients and to compare the interventions to each other, and then, we will perform a qualitative study to assess the experiences of participants throughout the intervention period. In total, the overall aim of this study is which intervention is better for controlling anticipatory grief of family caregivers of cancer patients.

## Methods

### Participants

This mixed-methods study has an embedded explanatory design with one quantitative and one qualitative phase [35]. We will first conduct a four-arm randomized controlled trial to quantitatively evaluate the effects of (1) combined family-based dignity intervention and expressive writing, (2) family-based dignity intervention alone, (3) expressive writing alone, and (4) routine care on anticipatory grief of family caregivers of dying cancer patients. Then, we will assess the experiences of participants in the quantitative phase through qualitative interviews with them. In this single-center study, we will include family caregivers of dying cancer patients who refer to the oncology center of Firozgar hospital affiliated to the Iran University of Medical Sciences, Tehran, Iran, to receive medical and palliative care for their patients.

### Inclusion criteria

We will include caregivers with the following criteria: (1) caregivers who are the first-degree relatives [i.e., parents, offspring, and siblings] of cancer patients and have the most responsibility for caregiving of them during the last 3 months, (2) those who are caregiving of the cancer patients who are dying or critically ill according to the opinion of the treating physician, and (3) caregivers aged ≥18 years.

### Non-inclusion criteria

We will not include caregivers who have a history of psychological disorders and those who have a history of death among their first-degree relatives. Also, caregivers who are not the first-degree relatives of dying cancer patients and those who have experience of psychological interventions (particularly dignity and expressive writing interventions) during the last 6 months will not be included. Also, we will exclude those caregivers who are not willing to continue each phase (quantitative and qualitative) throughout the study. Figure 1 shows the study flowchart.

**Fig. 1 Fig1:**
[figure not shown]
Study flowchart

### Ethics

All caregivers will read the terms written in informed consent, and optionally, they can accept to participate in the current study (Supplemental File 1). Principal investigators (MR and [name]) will be responsible for obtaining informed consent. The ethics committee of the Iran University of Medical Sciences approved the study (code: IR.IUMS.REC.1399.1097). Moreover, the quantitative phase of this study that is a randomized clinical trial was registered in the Iranian Registry of Clinical Trials (www.irct.ir) with code IRCT20210111050010N1.

### Study design for the quantitative phase

In the first phase of the current study (quantitative), a four-arm randomized controlled trial will be done. After recruiting family caregivers of dying cancer patients according to the inclusion criteria, they will be randomly assigned to one of the four groups: family-based single dignity intervention (group 1), expressive writing intervention (group 2), combined family-based single dignity intervention and expressive writing (group 3), and controls (group 4). Recruitment and random allocation will be done simultaneously. Allocation concealment will be done using the blocked randomization method. For this, we will use six blocks, each with a block size of 4 (A: group 1, B: group 2, C: group 3, and D: group 4), that the order of the letters in these blocks will be different (e.g., ABCD, ACDB). Then, a code ranging between 1 and 6 will be assigned to each of these six blocks. For allocating each four caregivers, at first, we will select one of the six blocks using random numbers obtained from an online randomizer (https://www.randomizer.org), and then, caregivers will be assigned to the four intervention groups according to the order of letters in the selected block. To ensure sufficient participant recruitment to reach the required sample size, recruitment and random allocation will continue until all groups become complete. Therefore, the enrollment period may extend over 12 months. It should be noted that random allocation will be done by a person who is unaware of the aim of our study.

After the random allocation, sessions related to the interventions (family-based single dignity intervention and expressive writing) will take place at the time that will be set with caregivers. To avoid sharing experiences between caregivers, we will try to provide a situation that caregivers do not have contact with each other. For this, we will include a maximum of four caregivers in a day from different rooms of the oncology center in Firozgar hospital (study setting) and we will set a specific time for each caregiver so that there is no possibility of contact and sharing experiences with each other. Also, after discharging the four previously included caregivers from the hospital, we will include the other new four caregivers to minimize their contact. On the other hand, recruitment will be stopped until discharging the four previously included caregivers. Caregivers in all intervention groups will receive routine care such as family counseling and meaning therapy, and they will be asked not to participate in other psychotherapy programs. Since the interventions used in the current study are interview-based, we cannot blind the investigators and caregivers to the interventions.

Before the intervention session and 1 week and 2 weeks after the interventions, anticipatory grief will be assessed by a 13-item anticipatory grief scale (AGS-13). The mean of AGE-13 score at baseline and throughout the study will be considered as the main outcome variable. The diagram for Standard Protocol Items: Recommendations for Interventional Trials (SPIRIT) is shown in Fig. 2.

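### Blocking is named as the concealment method, and six fixed orders of four, matched to recruitment batches of four, make assignments guessable if caregivers are enrolled one at a time

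*Protocol article*

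**What the plan says.** All of this is in the protocol article, mainly under Study design for the quantitative phase.

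- **Concealment.** "Allocation concealment will be done using the blocked randomization method".
- **The blocks.** "we will use six blocks, each with a block size of 4", and "that the order of the letters in these blocks will be different (e.g., ABCD, ACDB"). Further, "a code ranging between 1 and 6 will be assigned to each of these six blocks", and for each four caregivers "we will select one of the six blocks using random numbers obtained from an online randomizer".
- **Timing.** "Recruitment and random allocation will be done simultaneously". The same section also speaks of assigning caregivers once they have been recruited.
- **Batches.** Recruitment pauses until a group of four has left, and "after discharging the four previously included caregivers from the hospital, we will include the other new four caregivers to minimize their contact".
- **Blinding.** "we cannot blind the investigators and caregivers to the interventions". The Ethics section makes the principal investigators responsible for obtaining consent.
- **Allocator.** A separate person, who does not know the purpose of the study, carries out the allocation.

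**The concern.** Blocking is a way of generating a sequence. Concealment is a way of keeping the next assignment from those who decide whom to enrol. Naming the first as the second leaves the stated plan without concealment, and small fixed blocks work against it because the last places in a block follow from the earlier ones.

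Two features add to this. Only six orders are used where four arms allow 24, so the remaining places can be inferred sooner. And the block size equals the recruitment batch, so staff can see where each block starts and ends.

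At stake is selection bias at enrolment. Eligibility includes the treating physician's judgement that the patient is dying or critically ill, and the team chooses whom to approach and in what order. The people obtaining consent are not blinded, and the outcome is an unblinded self-report. An allocator who does not know the study's purpose does not stop the enrolling investigators from predicting the next arm.

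**Working it through.** **The plan's own figure.** The article gives no figure for predictability, but its sample size fixes the number of blocks. From Sample size calculation: n = 2 × (1.96 + 0.842)² × 23.1² / (78.17 − 64.49)² = 44.77, rounded up to 45. Allowing for 10% drop-out, 45 / 0.9 = 50 per group. That reproduces the stated 50, so 200 caregivers make 200 / 4 = 50 blocks.

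**Number of orders.** Four arms, each once per block: 4! = 24. The plan uses 6.

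**Odds at a position.** I assume each code from 1 to 6 is equally likely. If an arm stands at a given position in k of the six orders, its probability there is k/6. A probability of 1/4 needs k = 1.5, which is impossible. I enumerated all C(24,6) = 134,596 sets of six orders. In 125,896 of them (93.5%) at least one arm can never occur at some position. The most even sets have 1/6 or 2/6 in every cell. Each block still contains every arm once, so the totals stay at 50 per arm.

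**Guessing without the list.** Assume one-by-one enrolment with earlier assignments in the block visible. An observer who picks at random among the arms not yet used is right with probability 1/4, 1/3, 1/2 and 1 at the four positions, whichever orders are in use. The mean is (1/4 + 1/3 + 1/2 + 1) / 4 = 52.1%. The fourth assignment is certain, which makes 50 of 200.

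**Guessing with the list known.** At each position the observer names the arm most frequent among the orders that fit what has been seen. As an illustration that includes both example orders, take ABCD, ACDB, BCDA, BADC, CDAB and DABC:

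- Position 1: A and B each lead two orders, so 2/6.
- Position 2: after A or B there are two candidates, and after C or D only one. One correct guess for each first letter gives 4/6.
- Positions 3 and 4: the first two letters identify the order, so 6/6 each.
- Mean: (2 + 4 + 6 + 6) / 24 = 18/24 = 75%. Fully determined: (0 + 2 + 6 + 6) / 24 = 58.3%.

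Over all 134,596 sets the guess rate takes only three values: 17/24 = 70.8% (16,444 sets), 18/24 = 75.0% (95,688 sets) and 19/24 = 79.2% (22,464 sets). The mean is 75.2%. The 7,315 sets that contain both example orders have the same range and, to one decimal, the same mean.

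| Situation (earlier assignments in the block visible, except for chance) | Pos. 1 | Pos. 2 | Pos. 3 | Pos. 4 | Mean |
|---|---|---|---|---|---|
| Chance | 25% | 25% | 25% | 25% | 25% |
| All 24 orders, or the six not known | 25.0% | 33.3% | 50.0% | 100% | 52.1% |
| Six orders known, average over all sets | 43.6% | 68.1% | 89.1% | 100% | 75.2% |

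The share of assignments known with certainty is 33.3% to 62.5% with a known list (mean 53.2%), against 25% with all 24 orders.

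**Learning the list.** In 3,000 simulated trials of 50 blocks, an observer who starts without the list and keeps a record of past assignments guessed 72% correctly over the whole trial and 75% in the second half. All six orders had appeared after a median of 13 blocks.

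**The case against.** The strongest reply is that four caregivers may be enrolled together before their block is drawn. The article speaks of assigning caregivers after recruiting them, draws one block for each four, and brings in the next four as a group. If all four are consented and placed in a fixed order before the draw, neither 52% nor 75% applies at enrolment; only the uneven odds by position remain. This stands. The statement that recruitment and allocation are simultaneous points the other way, and the text does not settle it.

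Second, a separate person allocates, and an article may leave envelopes or custody of the list to the full protocol. That also stands, and the absence of envelopes is not counted here. The point rests on what the article states: it names a concealment method, and that method does not conceal.

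Third, a reader might infer more than the documents support:

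- **That 75% of assignments are predictable outright.** The 75% is an expected guess rate, and it needs recruiters who see earlier assignments and who know or learn the six orders. Nothing says they are shown the list.
- **That the arms are unequally allocated.** The uneven odds concern position within a block, and they matter only if caregivers are ordered with knowledge of the list.
- **That the first caregiver in every batch gets group 1**, because both example orders begin with A. Exactly 3! = 6 orders do, but the two are given only as examples. The set of all six is one of 134,596, or one of the 7,315 that contain both examples.
- **That selection bias would go unnoticed.** Baseline AGS-13 and demographic data are collected, groups are compared by ANOVA and chi-square, and ANCOVA adjusts for baseline and for variables that differ. Selection on measured grief could show and be partly adjusted for; selection on unmeasured traits would be hard to detect.

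**Conclusion.** The concern holds in a conditional form. Two parts need no assumption about enrolment: blocking is stated as concealment, which it is not, and the block size of four coincides with the recruitment batch. A third, that six orders cannot give any arm probability 1/4 at any position, needs only the equal-probability draw.

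The size depends on the enrolment sequence. With one-by-one enrolment and visible assignments, one assignment in four is certain and at least 52% can be guessed; with the six orders known or learned, 71–79%. If each batch is complete and ordered before its draw, prediction at enrolment largely disappears. The documents do not establish that selection will occur or that any particular six orders are in use. Since selection at enrolment cannot be fully repaired in the analysis and the correction is cheap, the rule should be changed.

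**What to change.** 1. Replace the sentence that equates blocking with concealment by a description of how assignments are kept from recruiters.
2. Have a person independent of recruitment generate the whole list in advance, either from all 24 orders or as fully random permutations in blocks of randomly varying size such as 4 and 8. Keep the list and the block sizes from recruiters.
3. Release each assignment, for example by sequentially numbered opaque sealed envelopes, only after eligibility, consent and baseline AGS-13 are complete.
4. Complete consent and baseline and fix the order for all four caregivers of a batch before any assignment in that batch is revealed. Varying the block size is not enough by itself: a balanced four-arm block is always a multiple of four, so it still ends on a batch boundary. Using all 24 orders alone restores 1/4 at each position but leaves the 52% guess rate under one-by-one enrolment.

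The cost is slightly more administration and a short delay before a batch's first session. With blocks larger than four, a batch may not contain every arm.

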#### Other information

Demographic data including age, sex, marital status, education, medical history, and medication will be collected at the baseline.

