### Statistical analysis for the quantitative phase

All collected data will be coded and then will be entered into the SPSS software version 18 (SPSS, Inc., Chicago, IL, USA) for performing statistical analysis. To ensure the accuracy of the dataset, it will be double-checked by another investigator. The analyses will be performed on the basis of an intention-to-treat (ITT) approach. Therefore, missing values will be treated according to the last-observation-carried-forward method. The Kolmogorov-Smirnov test will be used to examine the normal distribution of quantitative variables. We will normalize the non-normally distributed variables using log transformation. To detect differences in quantitative and categorical variables between the intervention groups, we will use the analysis of variance (ANOVA) and chi-square test, respectively. To determine the effect of family-based dignity intervention and expressive writing on anticipatory grief, we will use repeated measures ANOVA. In this analysis, the intervention groups (family-based dignity intervention, expressive writing, combined intervention, and control groups) will be considered as the between-subjects factor and the time points (before and 1 week and 2 weeks after the interventions) will be considered as the within-subjects factor. Also, to assess differences between the intervention groups in terms of mean changes of anticipatory grief, the multivariate analysis of covariance (ANCOVA) will be applied by considering baseline measurements and variables different between the groups as covariates. *P* value<0.05 will be considered as a significant level.

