### Limitations

Despite using validated questionnaires for the assessment of anticipatory grief, misclassification of caregivers in terms of this variable cannot be fully excluded. Since the interventions used in the current study are interview-based, we cannot blind the caregivers to the interventions. Although we try to control for variables different between the groups in statistical analysis, we cannot entirely exclude the effects of residual confounders or differences on our findings.

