## Data Availability

Only investigators will have access to the final trial dataset.

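### The reason given for not blinding investigators covers session staff only, yet as worded it also takes in those who check and analyse the data (minor)

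*Protocol article*

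**What the plan says.** Under Study design for the quantitative phase, the article opens its blinding sentence with the reason, "Since the interventions used in the current study are interview-based", and concludes that "we cannot blind the investigators and caregivers to the interventions". It exempts no role. The same section has a separate person, who does not know what the study is testing, do the random allocation. It also states which of the letters A to D stands for which of groups 1 to 4.

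Under Statistical analysis for the quantitative phase, data are coded and entered into SPSS and then "it will be double-checked by another investigator". Coding here describes data entry, and nothing is said about hiding the arm. Data Availability adds: "Only investigators will have access to the final trial dataset".

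The analysis section also contains steps that depend on the data. One is "We will normalize the non-normally distributed variables using log transformation", which follows a Kolmogorov-Smirnov test. Another is an ANCOVA "considering baseline measurements and variables different between the groups as covariates". Repeated measures ANOVA and ANCOVA are both named for anticipatory grief, and neither is called primary.

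Limitations gives the same reason again, but only for caregivers: "we cannot blind the caregivers to the interventions".

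**The concern.** The stated reason is narrower than the conclusion drawn from it. How a session is delivered decides whether the caregiver and the person delivering it can be blinded. It has no bearing on whether someone working on questionnaire totals sees the arm's name or a neutral code.

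In a trial with unblinded caregivers and a self-reported outcome, masked data handling is one of the few protections still available. The article's wording appears to rule it out without a reason that applies.

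Two things are at stake. A query or correction made during data checking could favour an arm the checker recognises. Decisions on scale, covariates and emphasis between the two models could also be made knowing which arm they help. The trial asks which intervention is better and judges each against routine care, so knowing the direction of a difference matters.

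**Working it through.** **1. Does the reason cover each role?**

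| Role | Where described | Does the reason apply? |
|---|---|---|
| Caregiver | Study design for the quantitative phase; intervention sections | Yes |
| Staff who hold the dignity session, teach the writing, make reminder calls or receive manuscripts | Intervention sections | Yes in substance, although expressive writing is done by the caregiver alone and is not an interview |
| Person allocating | Study design for the quantitative phase | Must know the sequence; is unaware only of the study's aim |
| Person double-checking the dataset | Statistical analysis for the quantitative phase | No |
| Analyst | Not named; only investigators hold the dataset (Data Availability) | No |

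The reason fails for the last two roles. They fall under the statement only if *investigators* means the same people in all three sections. That is the natural reading, but it is an inference.

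**2. Do Study design and Limitations conflict?** No. Limitations names caregivers and says nothing about whether investigators can be blinded. It is a shorter restatement.

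**3. Does any planned figure change?** The plan's own sample size reproduces:

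n = 2 × (1.96 + 0.842)² × 23.1² / (78.17 − 64.49)² = 44.77, rounded up to 45; 45 / 0.9 = 50 per group; 4 × 50 = 200.

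Masking does not enter this formula, so nothing changes.

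**4. How much do the analysis rules depend on the data?** Six baseline variables are listed under Other information: age, sex, marital status, education, medical history and medication. Assume that each is tested at 0.05 and that the tests are independent; the article states neither. The chance that at least one differs between properly randomised groups is

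1 − 0.95⁶ = 1 − 0.735 = 0.265.

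The covariate set would then change by chance in about a quarter of such trials. This holds whether or not the arm is masked.

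**5. Would masking change the error rate of the four-arm tests?** No. An omnibus F test uses the between-group sum of squares, Σ n_g (ȳ_g − ȳ)². Relabelling the groups only reorders the terms of that sum. In one simulated trial with no effect, the ANCOVA P value was 0.29282 both before and after the arm codes were permuted. Masking hides which arm is favoured and leaves the set of omnibus P values as it was.

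**The case against.** The strongest reply is that the blinding sentence closes a paragraph about arranging and delivering sessions, so *investigators* there means staff who meet caregivers. On that reading the article merely names no masked analyst, which an article may leave to a fuller document that is not shown. Part of this stands: the analyst's knowledge of the arm is inferred. But the word is unqualified, and the same word is used for the person who checks the data and for those who hold the dataset. A fuller document that named a masked investigator as analyst would conflict with the sentence as written. What remains is an over-broad statement, not silence.

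A reader might also infer that unmasked analysis pushes the false-positive rate well above 5%. The documents do not support that:

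- In a simulation with no effect (4000 trials, 4 × 50 caregivers, correlation near 0.6, six independent covariates tested at 0.05, all assumed), following the stated rules gave a week-2 ANCOVA error of 4.9%, the same as a fixed raw-score ANCOVA.
- Taking the better of that ANCOVA and the repeated measures group effect gave 9.6%. This comes from naming two models. By step 5 of the working, a masked analyst would face the same figure. The remedy is to pre-specify the covariates and one primary model.

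A reader might further infer that the analyst is free to choose scale and covariates. The article gives rules for both. They depend on the data, and no threshold is given for the covariates, but they are not an open choice.

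Finally, masking may be weak in practice. Nothing shows that the analyst is separate from those who ran sessions or collected manuscripts, and such a person might recognise caregivers from their records. That stands as a limit on the benefit.

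**Conclusion.** The point holds, with minor severity. The blinding statement is justified for caregivers and session staff and unjustified for checking and analysing questionnaire totals. Read with the data-checking and data-access statements, it places the data handlers among those declared impossible to blind.

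The gain from correcting it is specific: it guards against corrections or choices that favour a known arm. The documents give no basis for putting a number on that gain. Correcting it would not touch the main bias, which is self-report by unblinded caregivers and which the article discloses. It would not make the transformation and covariate rules less dependent on the data, and it would not reduce the multiplicity from naming two models.

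The conclusion rests on one assumption: that *investigators* has the same meaning in the blinding, data-checking and data-access statements.

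**What to change.** 1. In Study design for the quantitative phase, limit the statement to caregivers and to those who deliver the interventions. Word Limitations to match.
2. In Statistical analysis for the quantitative phase, state that data cleaning and analysis use neutral arm codes. These must not be A to D or groups 1 to 4, because the article gives their meaning.
3. State that the person who does the allocation holds the key and releases it only once the data are clean and the covariates, the outcome scale and one primary model are fixed. Fixing these in advance is also the remedy for the data-dependent rules and the two competing models, which masking alone would not cure.
4. Say whether the analyst also delivers sessions or collects manuscripts. If so, describe the masking as partial.

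The cost is about two sentences, a recoded arm variable and the safekeeping of a key. The key holder already exists in the plan. Whether a separate analyst is available cannot be told from the article. Sample size, alpha and power stay as they are.
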